## Trial status

This study is currently recruiting patients. The project started in August 2014. As we need around 18 months to finish each phase, we expect the study to finish end 2017.

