### Study design

The development of a CPR consists of three consecutive phases. The first two are the derivation and validation phase.

In the derivation phase a CPR is derived from a number of variables that have predictive potential for therapy outcome. These variables are obtained from baseline measurements and have a multidimensional character (impairments, activities and/or participation and contextual factors). Data analysis is being used to calculate the most powerful combination of these variables to finally form the new derived CPR (see Figure 1 and ‘Data analysis’).

In the validation phase the derived CPR will be applied in a new study population. This application will result in matched patients (allocated in accordance with the CPR) and in unmatched patients (not in accordance with the CPR). The treatment success of both groups will be compared. The hypothesis is that treatment success will be higher in the matched group (Figure 2).

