**Flow chart representing the design of the validation phase.**

For both phases, a single blinded randomized controlled trial study design will be used. The project started in August 2014. Analysis of these data is planned for the end 2015.

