#### Follow-up

Short-term follow-up will take place after completion of the treatment program at nine weeks. All primary and secondary outcome measures from the baseline testing will be reevaluated at this time point.

Long-term follow-up will take place at six months and one year after entering the study. The following outcome measurements will be inventoried: age, weight, hours of physical activity per week, profession, duration of LBP, MODI, Tampa scale for kinesiophobia and VAS. The patients will initially be contacted by mail, and by phone if they do not respond to the mail within two weeks to make an appointment (Table 3).

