#### Validation phase

In the validation phase new patients will be again assigned randomly into one of the three treatment groups. Based on the derived CPR determined in phase one, each intervention group will be divided into either ‘matched therapy’ or ‘unmatched therapy’. The recruitment, information form, informed consent, measurements, blinding and intervention procedure will be the same for both derivation and validation phase.

To verify intergroup differences at baseline, variables will be compared between groups using independent t tests, Mann-Whitney U tests, or chi-square tests of independence based on the nature of the data.

To examine the principle hypothesis (difference in treatment effect between matched and unmatched groups), a three-way repeated-measures analysis of variance will be performed with treatment group (motor control versus general active exercise therapy vs. isometric therapy) and classification subgroup (motor control versus general active exercise therapy versus isometric therapy) as between-subject variables and time (baseline, nine weeks, six months and one year) as the within-subject variable. The dependent variable is disability (MODI score). The hypothesis of interest is the three-way interaction, and the two-way interactions between time and treatment group and between time and classification subgroup. We hypothesize that outcome over time will not differ based on the randomized treatment group, or the classification subgroup, but will depend on the interaction between the treatment group and classification subgroup, such that patients randomized to matched treatment will have better outcomes than patients randomized to unmatched treatment. This hypothesis will be supported if the three-way interaction is significant, but the two-way interactions are not. Pairwise *post-hoc* comparisons will be performed at each follow-up period to further explore any significant interaction terms. In both the derivation and validation phase we will use an intention-to-treat analysis.

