Third, we aim to include a sufficiently large sample, based on a power analysis. Hicks *et al*. [16] included 54 patients in their study but no power analysis is mentioned in their paper. If there are not enough patients included, the CPR is unlikely to be valid. We compared our calculated sample size with the sample size calculated in Brennan *et al*.’s [17] study design and found comparable results. In addition, we use an extra 54% inclusion target to compensate for the possible dropout rate [34]. We aim to recruit 489 patients in total (combined total for both phases of the study). We calculated that each year around 200 LBP patients start the back revalidation program in the Antwerp University Hospital. This is the same for the Apra Rehabilitation Hospital. Out of these 400 LBP patients around 50% have nonspecific complaints. This means that we need around 18 months to finish each phase. We will closely follow the inclusion procedure to make sure we meet our goals. The current study protocol describes only the derivation and validation phase, and not the impact phase. Future research should target this impact phase. The impact phase needs a completely different approach since it investigates the economic consequences of the implication of the CPR. It also depends on the outcome of the derivation and validation phase. Consequently, it is beyond the scope of the present paper.

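### The stated finish of end 2017 leaves no room for the last validation patients' one-year MODI, and the end-2015 analysis date precedes the end of the derivation phase

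*Protocol article*

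**What the plan says.** - **Start and finish.** Trial status: "The project started in August 2014" and "As we need around 18 months to finish each phase, we expect the study to finish end 2017".
- **Where the 18 months comes from.** The Discussion counts about 200 back-pain patients per year at each of two hospitals, then says "Out of these 400 LBP patients around 50% have nonspecific complaints" and concludes "This means that we need around 18 months to finish each phase". The figure is built from patient flow.
- **Order of the phases.** Study design: "In the validation phase the derived CPR will be applied in a new study population". Randomization and blinding adds that validation patients are stratified by matched or unmatched status, so the rule must exist before the first of them is randomised.
- **Follow-up.** "Long-term follow-up will take place at six months and one year after entering the study". Table 3 lists MODI at both visits.
- **Use of the one-year value.** The Data analysis section for the validation phase has "time (baseline, nine weeks, six months and one year) as the within-subject variable".
- **Analysis date.** Study design, after Figure 2: "Analysis of these data is planned for the end 2015". The sentences just before it describe both phases.

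**The concern.** Two phases of 18 months from August 2014 end about August 2017. From there to the end of 2017 is four to five months, but the last validation patient needs twelve more months to reach the one-year MODI. No part of the article adds that year. The principal validation test is a repeated-measures analysis over four time points, so a team that held to the stated finish would run it while the latest entrants could not yet have a value at the fourth.

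The end-2015 date has a similar fault at the front of the study, since it falls before an 18-month derivation phase is over. It can only concern derivation data, because no validation patient would be enrolled by then. How far it misses depends on when treatment success is read. The derivation analysis defines success as a MODI decrease of six points but names no time point.

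**Working it through.** **Inputs from the article.** Start August 2014; about 18 months per phase; targets 260 and 229; flow 400 × 50% = 200 nonspecific patients per year; first follow-up at nine weeks (9/4.345 = 2.07 months); last follow-up at 12 months.

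**Assumptions.** Even accrual. The day of the start is not given, so 1 August and 31 August 2014 are both used. End 2015 is then month 17 or 16, and end 2017 is month 41 or 40.

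**1. The plan's own figures.** The targets reproduce: 120/(1 − 0.54) = 261 (stated 260), 105/(1 − 0.54) = 229, and 260 + 229 = 489. For the 18 months, 260/200 × 12 = 15.6 months of accrual, or 15.6 + 2.07 = 17.7 with the nine-week programme. For validation, 229/200 × 12 = 13.7 months. So the 18 months is recruitment, or at most recruitment plus nine weeks.

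**2. Could the 18 months include the one-year visit?** That would leave 6 months of accrual, or 6/12 × 200 = 100 patients, against targets of 260 and 229. It cannot.

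**3. Last one-year MODI and share not yet at one year by end 2017.** Let validation start at month s, accrue for d months, and let end 2017 be month e.

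- Last one-year visit = s + d + 12.
- Share without a one-year value if data closed at e = (s + d − (e − 12))/d.

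| Reading | s | d | Last visit (month) | Months after end 2017 | Share without one-year MODI |
|---|---|---|---|---|---|
| 18 months is accrual | 18 | 18 | 48.0 | 7.0–8.0 (about August 2018) | 7/18 to 8/18 = 39–44% (89–102 of 229) |
| 18 months includes the nine weeks | 18 | 15.93 | 45.9 | 4.9–5.9 (about June 2018) | 4.93/15.93 to 5.93/15.93 = 31–37% (71–85 of 229) |
| All 200 per year enrol, nine-week gap before validation | 17.67 | 13.74 | 43.4 | 2.4–3.4 (mid-March to mid-April 2018) | 2.41/13.74 to 3.41/13.74 = 18–25% (40–57 of 229) |

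Even with 200 per year and no gap between phases, the last visit is at month 15.6 + 13.74 + 12 = 41.3, still 0.3–1.3 months late. That case is not feasible, because the rule must be derived first.

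**4. Derivation data at end 2015.**

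| | 18 months' accrual | Stated flow (15.6 months) |
|---|---|---|
| Enrolled | 16/18 to 17/18 = 89–94% | 100% |
| Nine-week MODI | 13.93/18 to 14.93/18 = 77–83% | 13.93/15.6 to 14.93/15.6 = 89–96% |
| One-year MODI | 4/18 to 5/18 = 22–28% | 4/15.6 to 5/15.6 = 26–32% |

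If success is read at nine weeks, the last visit needed comes after end 2015 by:

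- 17.67 − 17 to 17.67 − 16 = 0.7–1.7 months at the stated flow;
- 18 − 17 to 18 − 16 = 1–2 months if the 18 months includes the nine weeks;
- 20.07 − 17 to 20.07 − 16 = 3.1–4.1 months at 18 months' accrual.

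**The case against.** The best defence is that these are calendar forecasts, worded as expectations, and that they alter no endpoint, sample size, visit or analysis. The follow-up section, Table 3 and the validation analysis all commit every patient to a one-year MODI, so the natural result of the error is a later finish. At the stated flow the slip is only about two and a half to three and a half months. This stands as to consequence and severity. It does not reconcile the dates, since no feasible reading puts the last one-year visit inside 2017.

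Four stronger readings are tempting but not supported:

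- **That a large share of one-year data will be lost.** Nothing stops follow-up or closes the data at end 2017. The shares above are conditional on that.
- **That half or more of validation patients would lack the value.** This comes from adding nine weeks to 18 months of accrual: s = 20.07 and d = 18 give 50–56%. Since 15.6 months plus nine weeks is already 17.7, the nine weeks may be counted twice.
- **That the rules will be derived from an incomplete phase.** The article does not say the analysis would go ahead without the remaining patients. If success is read at nine weeks, the date misses by one to a few months.
- **That the accrual figure is too optimistic.** Enrolling 260 of the 300 nonspecific patients seen in 18 months means 87%, which looks demanding. But the article gives no eligibility, refusal or preference rates. Most Table 2 exclusions also concern possible specific disease, so many such patients may already lie outside the nonspecific half.

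**Conclusion.** The concern holds as a contradiction between dates. An August 2014 start, two sequential phases of about 18 months and a one-year MODI in the principal validation analysis put the last required visit between about mid-March and August 2018, depending on what the 18 months covers. End 2017 fits the end of recruitment only.

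If, and only if, the data were closed at end 2017, between about 18% and 44% of validation patients would have no one-year value by calendar alone. The end-2015 date precedes the end of an 18-month derivation phase. It is a near miss if success is read at nine weeks, and cannot hold if success is read at one year; the article does not say which.

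The sizes rest on even accrual and an unknown start day within August 2014. The lowest range also needs every nonspecific patient to enrol. Severity is minor to moderate: the dates are wrong as written, but easily corrected.

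**What to change.** Reconcile the Study design, Discussion and Trial status sections:

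1. Say whether 18 months means recruitment only or recruitment plus the nine-week visit.
2. Name the time point at which treatment success is read, and date the derivation analysis after the last derivation patient's visit at that time point.
3. Give separate dates for the end of validation recruitment and for the last one-year visit (last validation patient in plus 12 months).
4. State that the principal validation analysis is not run before that last visit.

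The cost is a change of wording and a later stated end date. The one-year follow-up is already planned, so no patients, visits or procedures are added.

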### Consent

Written informed consent was obtained from the patient(s) for publication of this manuscript and accompanying images. A copy of the written consent is available for review by the Editor-in-Chief of this journal.

## Abbreviations

CI: Confidence interval
CLBP: Chronic low back pain
CPR: Clinical prediction rule
FABQ: Fear Avoidance Believe Questionnaire
LBP: Low back pain
LR: Likelihood ratio
MODI: Modified Oswestry Disability Questionnaire
RMDQ: Roland Morris Disability Questionnaire
SF36: Short Form 36 Health Survey
VAS: Visual Analogue Scale.
